### The PIL-FAST 'trial pack'

In order to enable access to study medication and the necessary administration equipment in the pre-hospital setting, boxes of lisinopril and matched placebo, along with other study materials, have been secondarily packaged into a 'trial pack'. The trial pack contains the paramedic research paperwork, study medication, a syringe crusher, a 5 ml syringe and 5 ml vial of water. Each pack carries a unique study number which matches the medication box number (linked to the randomisation code). Packaging of trial packs was carried out by the Newcastle upon Tyne Hospitals Pharmacy Production Unit.

The provision of trial packs to research trained paramedics mirrors the provision of routine ambulance drug supplies to the North East Ambulance Service which are provided by Lloydspharmacy, a community pharmacy, in weekly deliveries to ambulance stations. Once packaged by the Newcastle upon Tyne Hospitals Pharmacy Production Unit, the trial packs were transferred to the local Lloydspharmacy in Gateshead who are storing and delivering the packs to participating North of Tyne ambulance stations. Lloydspharmacy delivery staff place packs in the ambulance station drug rooms and replenish to meet a minimum stock supply on their weekly visit to restock routine drug supplies.

A trial pack is collected by each research trained paramedic, taken into their ambulance service vehicle and carried on their emergency shift. If the pack is unused at the end of the shift, it is stored in the paramedic's individual secure locker until their next shift. This approach is being employed due to the logistics of drug storage on ambulance service vehicles and because the vehicles will not always carry a research trained paramedic. Second and subsequent packs are collected once the first pack has been used. Packs are opened after an eligible patient gives consent to take part in the trial and contents accompany the participant to hospital.

In addition to the contents listed above, 20% of the trial packs also contain a small temperature monitoring device. This is because ambulance service vehicles do not contain temperature controlled storage spaces and trial medication should not be stored above 25°C. Temperature monitoring is also being performed in a sample of ambulance station storage areas which similarly are not routinely temperature controlled.

### Paramedic training

Paramedics taking part in the study are volunteers from the NEAS North of Tyne division. In order to participate, they must have attended a training day which covered the principles of Good Clinical Practice (GCP), stroke recognition and trial eligibility assessment, the trial consent process and other trial procedures. In addition, all research trained paramedics have been issued with a small laminated booklet, designed to be carried on emergency shifts, which details inclusion and exclusion criteria, the consent script and emergency contact numbers.

### Randomisation

Treatment allocation is according to the trial pack carried by the recruiting paramedic. The trial packs carry unique study numbers identical to the numbers on the boxes of lisinopril and matched placebo contained within. The numbers are according to a master randomisation list created by an independent statistician. Intervention and control allocations are in 1:1 ratio.

### Blinding

Participants, clinicians (paramedics, investigators, outcome assessors) and other trial staff are blinded to treatment allocation. Lisinopril and placebo tablets are identical in appearance and packing. In the event of an emergency (as confirmed by the local site investigator, chief investigator or emergency doctor if investigators unavailable), the on-call pharmacist at the trial pharmacy can be contacted to reveal treatment allocation.

The integrity of blinding is checked at the final participant assessment. The participant is asked if they believe they received lisinopril or placebo. The assessor is also asked to record the treatment that they believe the participant to have received.

### Baseline data

In addition to the baseline eligibility data collected by research trained paramedics, the following are collected from routine records by a member of the hospital stroke research team following arrival of the participant at hospital: place of residence, past medical history, medication prior to admission, stroke type, brain imaging result, electrocardiogram result (rate, rhythm, voltage criteria for left ventricular hypertrophy (LVH)), renal function (urea and creatinine) on admission.

The following assessments are also performed within 18 hours of admission to hospital:

• Pre-stroke Barthel ADL Index score [24]

• Pre-stroke Modified Rankin Scale score [25]

• National Institute of Health Stroke Scale score [23]

Furthermore, at the hospitals taking part in this research study, the stroke research teams routinely screen the records of all patients admitted with a diagnosis of suspected acute stroke. Data from this screen is being used to identify all patients who fulfilled the study eligibility criteria and those that were transported to hospital by a research trained paramedic. For patients transported to hospital by a research trained paramedic and study eligible but not enrolled, paramedic routine clinical records are examined and any details about study screening or approach recorded if available.

In order to assess the additional time spent on scene by paramedics enrolling trial participants, time from arrival on scene to hospital door is obtained for all stroke admissions to the research hospitals from NEAS data records.

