### Secondary objectives

• To report the proportion of suspected acute stroke patients admitted to research sites during the trial duration who fulfilled the study eligibility criteria.

• To report the proportion of study eligible patients attended by a research trained paramedic.

• To report the proportion of study eligible patients enrolled into the study by a research trained paramedic.

• To report the proportion of study eligible patients approached about the research study but not enrolled, and to report reasons for non-enrolment where possible.

• To report the proportion of study eligible patients not approached about the research study, and to report reasons for non-approach where possible.

• To determine the additional time spent on scene by research trained paramedics to enrol a participant into the study.

• To report paramedic compliance with study data collection.

• To report hospital staff compliance with study medication administration and data collection.

• To report the proportion of study participants with confirmed stroke who complete seven days of study medication.

• To collect and report completeness and summary statistics on clinical data to inform the design of a definitive multicentre randomised controlled trial:

- change in blood pressure in intervention and control groups for 7 days post stroke

- change in neurological score (National Institute of Health Stroke Scale [23]) in intervention and control groups at 3 and 7 days post stroke

- dependency score (Barthel Activities of Daily Living (ADL) Index [24], Modified Rankin Scale [25]) in intervention and control groups at 7 days post stroke

- change in renal function in intervention and control groups at 7 days post stroke

- mortality in intervention and control groups at 7 days post stroke

• To report adverse events in control and intervention groups during the study.

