### Study setting

The study is being undertaken by the North East Ambulance Service NHS Trust (NEAS), Newcastle upon Tyne Hospitals NHS Foundation Trust (Royal Victoria Infirmary) and Northumbria Healthcare NHS Foundation Trust (two sites, North Tyneside General Hospital and Wansbeck General Hospital). The study is initiated in the community by NEAS research trained paramedics, including administration of the first dose of study medication. The NEAS workforce is divided into geographical regions and the study is active in the North of Tyne division where patients are transported to the Newcastle or Northumbria hospitals which are taking part in the pilot trial. The North of Tyne division covers a population of approximately 500,000 and admits around 1200 patients with suspected stroke per year.

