#### Inclusion criteria

• Adults ≥ 40 years old

• New unilateral arm weakness thought to be due to acute stroke within 3 hours of symptom onset

• Hypertension as defined by systolic BP >160 mm Hg on two consecutive seated or lying readings taken 5 - 10 minutes apart

• Conscious (eyes open spontaneously i.e. "A" on Alert, Voice, Pain, Unresponsive (AVPU) scale)

• Patient being transported to a PIL-FAST trial site (i.e. Royal Victoria Infirmary, North Tyneside General Hospital or Wansbeck General Hospital)

• Verbal consent obtained from participant or next of kin

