#### Assessment and consent in the pre-hospital setting

The routine clinical assessment of patients with acute stroke by paramedics (i.e. symptoms and signs of stroke, physiological observations, previous medical history, current medications and drug sensitivities) provides the information needed to determine whether a patient fulfils the study inclusion and exclusion criteria. Confirmation of fulfilment of the eligibility criteria is recorded on the study case record form (CRF) following consent to enter the study.

If a potential participant meets the inclusion criteria, a simple explanation of the study is provided verbally by the attending research trained paramedic as follows:

• Your symptoms suggest you have had a stroke.

• Your blood pressure is high.

• We are working with doctors at Newcastle University to find out if it is possible to use a blood pressure lowering treatment before patients reach hospital.

• In some people this might improve recovery after stroke, but it is not proven.

• Would you be willing to take part in a study to help?

• This means receiving a small dose of a blood pressure lowering tablet or an identical "dummy" tablet before reaching hospital. The type of tablet people receive is decided by chance.

• You will be offered one or two of these extra tablets for the next seven days.

• If you agree to take part then you will be told more about the study at hospital and given the option to pull out if you change your mind.

• Your treatment and care will not be affected if you decide not to take part.

Following this explanation the research trained paramedic assesses the understanding of the potential participant by asking three questions as below.

Can I check you understood what I said about the study?

• What do we think is wrong with you at the moment? [answer: stroke]

• What did I say about your blood pressure? [answer: high]

• What will you receive if you do help with the study? [answer: tablet]

An opportunity to ask questions is then provided. The research paramedic asks "Do you have any questions about the study?" The patient is then asked to provide verbal confirmation that they are happy to take part. The consent process takes approximately three to five minutes. A longer consent process would delay transfer to hospital. Verbal confirmation of consent is recorded on the paramedic signed CRF. Following verbal consent, the patient enters the study and receives the first dose of study medication.

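### The objective is extra time on scene, but the interval obtained runs to the hospital door, so the journey is mixed into an expected effect of a few minutes

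*Protocol article*

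**What the plan says.** Under Secondary objectives, the protocol article lists this aim: "To determine the additional time spent on scene by research trained paramedics to enrol a participant into the study". The Baseline data section returns to it with a purpose clause, "In order to assess the additional time spent on scene by paramedics enrolling trial participants", and then gives the data to be used: "time from arrival on scene to hospital door is obtained for all stroke admissions to the research hospitals from NEAS data records".

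The article does not mention a time of leaving scene, and it does not write out the comparison to be made. The same section says that hospital research teams screen all suspected stroke admissions. From that screen they identify who met the eligibility criteria and who was brought in by a research trained paramedic.

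Two other places bear on the size of the effect. Under Assessment and consent in the pre-hospital setting: "The consent process takes approximately three to five minutes". Under Inclusion criteria, hypertension must be shown "on two consecutive seated or lying readings taken 5 - 10 minutes apart".

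**The concern.** The purpose and the measure do not match. Time on scene ends when the ambulance leaves; the interval obtained ends at the hospital door. The journey is therefore part of every value, and selecting a subset of the records later cannot take it out.

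The reference group is a second, weaker difficulty. Participants are a selected group: alert, hypertensive, and with "New unilateral arm weakness thought to be due to acute stroke within 3 hours of symptom onset". Most stroke admissions would fail at least one criterion, and some of those criteria could plausibly affect how long a crew stays on scene. If enrolled patients were set against every admission, such differences would be read as enrolment time.

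The protocol itself treats minutes as important. It justifies the short consent process by the need not to delay transfer, and its Background cites the time dependence of thrombolysis. A figure for the time cost of enrolment should be able to resolve a few minutes and attribute them correctly.

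**Working it through.** The protocol gives no expected value, standard deviation (SD) or precision for on-scene time, so there is no planned figure to reproduce. The check has three parts.

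**1. Who would be in the reference group**

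Inputs from the protocol article:
- Study setting: the division "admits around 1200 patients with suspected stroke per year".
- Sample size calculation: about 200 eligible patients per year, and a target of 60 randomised.
- Current study status: start on 29 October 2010, recruitment to the end of December 2011. That is 428 days, or 428 / 30.4375 = 14.06 months.

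Results:
- Admissions: 1200 × 14.06 / 12 ≈ 1,406. Less 60 enrolled: about 1,346.
- Eligible: 200 × 14.06 / 12 ≈ 234. Less 60 enrolled: about 174.
- Eligible share of non-enrolled admissions: 174 / 1,346 ≈ 13%. About 87% are not eligible.

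**2. Bias**

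Apparent added time = true added on-scene time + difference in mean journey + difference in on-scene time due to case mix.

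The protocol puts consent at 3–5 min. If the second blood pressure reading would not otherwise have been taken, the wait of 5–10 min could bring the total to 15 min. The journey differences below are assumptions; the case-mix term is set to zero.

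| True added time (min) | Journey differs by ±2 min | Journey differs by ±5 min |
|---|---|---|
| 3 | 1 or 5 (67% error) | −2 or 8 (167%) |
| 5 | 3 or 7 (40%) | 0 or 10 (100%) |
| 15 | 13 or 17 (13%) | 10 or 20 (33%) |

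If mean journeys are equal, this bias is zero and only noise remains.

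**3. Precision**

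95% half-width = 1.96 × √(SD_scene² + SD_journey²) × √(1/60 + 1/n), where n is the size of the comparator. All SDs are assumptions. SD_scene is 10 min here.

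| Interval | n = 1,346 | n = 174 |
|---|---|---|
| On scene only | 2.6 min | 2.9 min |
| Scene to door, SD_journey 5 | 2.9 min | 3.3 min |
| Scene to door, SD_journey 10 | 3.7 min | 4.1 min |
| Scene to door, SD_journey 15 | 4.7 min | 5.3 min |

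Moving from 1,346 to 174 comparators widens the half-width by √(1/60 + 1/174) / √(1/60 + 1/1,346) = 0.150 / 0.132, or about 13%, whatever the SD. The 60 enrolled patients dominate the error. The noise that the journey adds depends heavily on the assumed SDs. For an on-scene SD of 7–15 min and a journey SD of 5–15 min, the variance is multiplied by between (15² + 5²) / 15² = 1.1 and (7² + 15²) / 7² = 5.6.

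**The case against.** The strongest reply is that the article describes a data extract, not an analysis. Times are obtained for all stroke admissions; nothing says that enrolled patients will be compared with all of them. The hospital screen allows a narrower comparison, and an analysis plan that is not shown may specify one. A reader might infer that all admissions are the declared comparator. The text does not support that; it is only the sole group named. This part of the objection stands for case mix. It does not answer the journey problem, which lies in the interval itself.

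A reader might also infer that enrolled patients have systematically different journeys. No passage shows this. No criterion restricts distance, and enrolled patients go to the same three hospitals whose admissions form the extract. Bias from the journey is possible, but it is not demonstrated and its direction is unknown.

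Scene-to-door time is also a sound measure of total pre-hospital delay, which is the protocol's own worry. The first dose has to be given before hospital but not expressly before departure, so an on-scene measure could miss trial activity during the journey. This stands, and is a reason to keep both intervals.

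Finally, an eligible, non-enrolled comparator is not clean. Some of these patients were approached, and their times may include explanation and consent. If eligibility is applied strictly, they also had the repeat reading, so that wait would cancel out of the contrast. Both points stand and shape the remedy.

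**Conclusion.** The mismatch holds. The stated objective concerns time on scene, and the stated interval does not measure it. The journey adds noise. It adds bias only if mean journeys differ: at an assumed 2 min, a true 5 min would appear as 3 or 7 min. The 13% eligible share follows from the protocol's own rates and shows how far an unrestricted comparison would be from like with like, though the article does not commit to that comparison. The half-widths rest entirely on assumed SDs.

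The issue is moderate. A reader might infer that a flaw in measuring delay to hospital must be corrected before the trial can be relied on. The documents do not support that: this is one descriptive secondary objective in a pilot. The primary objective of enrolling four patients per month and the randomised comparison do not depend on it.

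**What to change.** 1. Request the time of leaving scene from the same ambulance service records. The article does not say that it is held; this is assumed. Use arrival at scene to departure from scene as the measure for this objective.
2. Keep arrival at scene to hospital door as a separate measure of total pre-hospital delay.
3. Compare enrolled patients with the eligible, non-enrolled patients whom the hospital screen already identifies, by receiving hospital. Report separately those approached but not enrolled. State whether comparators had the repeat blood pressure reading, so that it is clear whether that wait is part of the estimate.
4. If departure times are not held, keep the scene-to-door interval with the same restricted comparator, and reword the objective as additional time to hospital.

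The cost is one more timestamp in an existing data request and a change of wording. The comparator falls from about 1,346 to about 174. For on-scene time at an assumed SD of 10 min, the half-width goes from about 2.6 to about 2.9 min, a small loss for a comparison closer to like with like.

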### Outcome assessments

Outcome data is collected from (i) routine clinical records and (ii) specific research assessments, by a member of the hospital stroke research team.

(i) Blood pressure during the first 48 hours following study entry is transcribed from routine clinical records onto the study CRF. Blood pressure at hospital admission, and at 4, 24 and 48 hours after admission is recorded (blood pressure is also recorded at the study medication dosage review, as above).

(iii) Specific research assessments take place at (a) day 3 after study entry and (b) day 7 (+/- 1 day) after study entry.

(a) On day 3 after study entry the following assessments are performed:

• Blood pressure (3 readings)

• National Institute of Health Stroke Scale

(b) On day 7 (+/- 1 day) after study entry the following assessments are performed:

• Blood pressure (3 readings)

• National Institute of Health Stroke Scale

• Barthel ADL Index

• Modified Rankin Scale

• Blood test for renal function, (urea, creatinine)

If a participant is discharged before day 3 or 7 following study entry, they will be asked to attend the outpatient department for data collection.

The study schedule is shown in Table 1.

**Table 1 T1:** Study schedule

	Day 1	Day 2	Day 3	Day 4	Day 5	Day 6	Day 7
Eligibility assessed by paramedic from routine clinical data	x						

Study discussed and verbal informed consent/assent obtained by paramedic	x						

Randomisation	x						

Further study information provided and written informed consent/assent obtained by hospital research team	x						

Appropriateness to continue study medication reviewed by hospital team	x						

Review of medical records to collect baseline stroke details and medical history	X						

Blood pressure measurements	x	x	x				x

National Institute of Health Stroke Scale	x		x				x

Barthel ADL Index (pre-stroke)	x						

Barthel ADL Index (post-stroke)							x

Modified Rankin Scale (pre-stroke)	x						

Modified Rankin Scale (post-stroke)							x

Blood test for renal function							x

Review of medical records to record concomitant blood pressure medications							x

Treatment with study medication	x	x	x	x	x	x	x

Review of study medication dosage	x						

Adverse Events	x	x	x	x	x	x	x

### Study withdrawal

No specific study withdrawal criteria have been pre-set. Participants may withdraw from the study at any time for any reason. Should a patient decide to withdraw from the study, a reason will be sought (to allow the study team to assess likely barriers to participation and retention) but patients can chose to withdraw without providing an explanation. Participants who chose to withdraw are monitored for adverse events for seven days after initiation of study medication. Patients wishing to withdraw prematurely from study medication are asked if they would be willing to continue with follow-up assessments as per the study schedule.

Investigators may also withdraw participants from the study at any time if they feel it is no longer in their interest to continue, for example, because of intercurrent illness or adverse events. Withdrawn participants are not replaced.

### Pharmacovigilance

The safety of lisinopril 5-10 mg in acute stroke will be evaluated by examining the occurrence of all adverse events as defined by the Medicines for Human Use (Clinical Trials) Regulations [31].

For serious adverse events (SAE), relationship to treatment (causality) and expectedness is determined by the local site investigator. Any queries will be discussed with the Chief Investigator. Excepting common and anticipated stroke complications (pneumonia, urinary tract infection, seizure, headache, deep vein thrombosis, pulmonary embolism), all SAEs will be reported to the co-ordinating centre immediately (within 24 hours) to comply with the Medicines for Human Use (Clinical Trials) Regulations [31]. Anticipated stroke complications need not be reported within 24 hours.

The Medicines and Healthcare products Regulatory Agency (MHRA) and ethics committee will be notified of all suspected unexpected serious adverse reactions (SUSAR) according to the following timelines in line with the Medicines for Human Use (Clinical Trials) Regulations: fatal and life threatening within 7 days of notification, non life threatening within 15 days. SUSARs will also be notified to all trial sites.

For non serious adverse events, local site investigators will determine relationship to treatment and data will be processed with routine trial data.

